## Abstract

**Background:**

Ticagrelor is an oral platelet P2Y12 receptor antagonist which is recommended for patients suffering from myocardial infarction, both with and without persistent ST segment elevation. Morphine is the first choice drug in pain alleviation in the same clinical subset. Recently a possible negative influence of morphine on the pharmacokinetics and antiplatelet effects of P2Y12 receptor blockers has been postulated.

**Methods/design:**

The IMPRESSION study is a phase IV, single center, randomized, double-blind, placebo-controlled clinical trial that is designed to assess the influence of morphine on the pharmacokinetics and pharmacodynamics of ticagrelor in patients with myocardial infarction. The study is planned to include up to 100 patients with myocardial infarction who will be randomized into one of two arms in a 1:1 ratio. Subjects in the intervention arm prior to the loading dose of ticagrelor (180 mg) will receive morphine (5 mg) intravenously, whereas patients in the control arm will receive a placebo prior to the loading dose of ticagrelor (180 mg). The pharmacokinetics of ticagrelor and its active metabolite (AR-C124910XX) will be assessed by liquid chromatography mass spectrometry. Platelet function testing in each patient will be performed using up to four different methods (platelet vasodilator-stimulated phosphoprotein assay, multiple electrode aggregometry, VerifyNow, and light transmission aggregometry).

**Discussion:**

This study is expected to provide essential evidence-based data on the impact of morphine on the absorption of ticagrelor in patients with myocardial infarction as well as to shed some light on the suspected connection between morphine use and antiplatelet activity of ticagrelor in the same group of patients.

**Trial registration:**

ClinicalTrials.gov identifier: NCT02217878 (14 August 2014).

## Background

Platelet activation and aggregation play a pivotal role in the pathophysiology of acute coronary syndromes (ACS), including ST-segment elevation myocardial infarction (STEMI) and non-ST-segment elevation myocardial infarction (NSTEMI). Dual antiplatelet therapy, consisting of aspirin and one of the P2Y12 receptor antagonists, constitutes the mainstay of ACS treatment. Achievement of adequate and timely platelet inhibition is of vast importance in the acute phase of myocardial infarction. Results of the PLATO trial have shown that therapy with ticagrelor, a novel platelet P2Y12 receptor inhibitor, compared with clopidogrel reduces not only the rate of death from vascular causes, myocardial infarction, or stroke, but also all-cause mortality, without concomitant increase in the rate of overall major bleeding, in patients with ACS [1,2]. The superiority of ticagrelor over clopidogrel evidenced in the PLATO trial has been principally attributed to ticagrelor’s fast, potent, and uniform pharmacodynamic features [2,3].

Based on the mentioned results, therapy with ticagrelor received class I B recommendation according to the European Society of Cardiology (ESC) in interventionally treated STEMI patients and in all moderate-to-high risk patients with ACS without persistent ST-segment elevation, including NSTEMI patients, regardless of initial treatment strategy [4,5]. Likewise, the American College of Cardiology Foundation and American Heart Association (ACCF/AHA) Task Force on Practice Guidelines recommend the use of ticagrelor in these subsets of patients [6,7].

The same ESC and ACCF/AHA guidelines recommend the use of morphine as a treatment of choice for pain relief in the clinical setting of myocardial infarction [4-6]. However, these recommendations, although strong, are only based on expert consensus. Pain relief in patients presenting with acute myocardial infarction (AMI) is suggested to lead to decreased sympathetic activation, thus preventing vasoconstriction and subsequent increase in the workload of the heart. Additionally, apart from its analgesic effects, morphine also alleviates the work of breathing and reduces anxiety [4,6]. On the other hand, despite its favorable analgesic and sedative actions, morphine also exerts adverse effects, which include hypotension, bradycardia, respiratory depression, vomiting, and reduction of gastrointestinal motility. Importantly, both the safety and efficacy of morphine have never been tested in randomized trials in the ACS setting, while a large, retrospective analysis of the CRUSADE registry suggests that morphine administration may be associated with increased mortality in patients with non-ST-segment elevation ACS [8]. Some of the previously listed side effects of morphine could affect the intestinal absorption and thus the pharmacokinetics (PK) and pharmacodynamics (PD) of orally administered drugs which are concomitantly used with morphine. Note that currently all commercially available P2Y12 blockers are oral agents.

In concordance with those facts, it was observed that morphine lags clopidogrel absorption, decreases plasma levels of clopidogrel and its active metabolite, and delays and diminishes antiplatelet effects of this thienopyridine, although this was observed in a group of healthy volunteers [9]. Moreover, Parodi *et al*. in their study comparing the PD of ticagrelor and prasugrel in STEMI patients reported that morphine administration may be associated with impaired antiplatelet effects of both investigated drugs [10].

However, a definitive evidence of a possible interaction between morphine and the novel P2Y12 receptor antagonists may be obtained only in randomized studies. At present, no PK and PD data regarding the concurrent use of morphine and P2Y12 blockers in the ACS setting are available. Therefore, evidence-based verification of morphine’s influence on the PK and PD of ticagrelor and its active metabolite (AR-C124910XX) could provide a valuable insight into the knowledge regarding modern ACS management.

## Methods/design

### Study objectives

The primary objective of the Influence of Morphine on Pharmacokinetics and Pharmacodynamics of Ticagrelor in Patients with Acute Myocardial Infarction (IMPRESSION) study is to test the hypothesis that intravenous administration of morphine prior to ticagrelor administration in patients with AMI alters the plasma concentrations of ticagrelor and its active metabolite.

The secondary objective of this study is to determine whether intravenous administration of morphine prior to ticagrelor administration in AMI patients attenuates the antiplatelet effects of ticagrelor.

Additionally, a predefined subanalysis has been planned to investigate which of the platelet reactivity assessment methods utilized in the study best reflects concentration of ticagrelor and its active metabolite.

### Study design and population

The IMPRESSION study is a phase IV, single center, randomized, double-blind, placebo-controlled, PK and PD clinical trial. The study population includes subjects presenting with AMI, including both STEMI and NSTEMI patients. After admission to the study center (Cardiology Clinic, Dr. A. Jurasz University Hospital, Bydgoszcz, Poland) and confirmation of the initial STEMI or NSTEMI diagnosis, patients will receive orally a 300-mg loading dose of plain aspirin and will be screened for eligibility for the study. The inclusion and exclusion criteria are as listed in Table 1. Eligible patients will be randomly assigned in a 1:1 ratio to one of two study arms. The patients in the intervention arm will receive 5 mg of morphine intravenously (IV) followed by a 180-mg loading dose of ticagrelor, whereas patients in the control arm will obtain 5 mg of a placebo IV followed by a 180-mg loading dose of ticagrelor (Figure 1). Subsequently all patients will undergo a coronary angiography followed by percutaneous coronary intervention (PCI), if necessary. Blood samples for PK and PD assessment will be drawn at eight predefined time points during the first 12 hours after randomization, according to the blood sampling schedule as presented in Figure 2. A telephone follow-up will be conducted at 30 days post-randomization, which will conclude the subject’s participation in the study.

**Table 1 Tab1:** **Inclusion and exclusion criteria for IMPRESSION study**

Inclusion Criteria	
Provision of informed consent prior to any study-specific procedures	Provision of informed consent for angiography and PCI
Diagnosis of acute STEMI or acute NSTEMI	Male or non-pregnant female, aged 18 to 80 years old
Exclusion Criteria	
Chest pain described by the patient as unbearable or patient’s request for analgesics	History of major surgery or severe trauma (within 3 months)
Prior morphine administration during the current STEMI or NSTEMI	Patients considered by the investigator to be at risk of bradycardic events
Treatment with ticlopidine, clopidogrel, prasugrel, or ticagrelor within 14 days before the study enrollment	Second- or third-degree atrioventricular block during screening for eligibility
Hypersensitivity to ticagrelor	Patient required dialysis
Current treatment with oral anticoagulant or chronic therapy with LMWH	History of asthma or severe chronic obstructive pulmonary disease
Active bleeding	Manifest infection or inflammatory state
History of intracranial hemorrhage	Killip class III or IV during screening for eligibility
Recent gastrointestinal bleeding (within 30 days)	Respiratory failure
History of coagulation disorders	History of severe chronic heart failure (NYHA class III or IV)
Concomitant therapy with strong CYP3A inducers (rifampicin, phenytoin, carbamazepine, dexamethasone, phenobarbital) within 14 days and during study treatment	Concomitant therapy with strong CYP3A inhibitors (ketoconazole, itraconazole, voriconazole, telithromycin, clarithromycin, nefazadone, ritonavir, saquinavir, nelfinavir, indinavir, atazanavir)
Hemoglobin concentration less than 10.0 g/dl	Platelet count less than <100 x10^3/mcl
History of moderate or severe hepatic impairment	Body weight below 50 kg

LMWH: low-molecular-weight heparin; NSTEMI: non-ST-segment elevation myocardial infarction; NYHA: New York Heart Association; PCI: percutaneous coronary intervention; STEMI: ST-segment elevation myocardial infarction.

**Figure 1 Fig1:**
[figure not shown]
Trial schema for the IMPRESSION study. Legend: IV: intravenous; PCI: percutaneous coronary intervention.

**Figure 2 Fig2:**

Blood sampling schedule for the IMPRESSION study.

The study will be conducted in accordance with the principles contained in the Declaration of Helsinki, and the study site received approval from the Local Ethics Committee to conduct the study (Komisja Bioetyczna Uniwersytetu Mikołaja Kopernika w Toruniu przy Collegium Medicum im. Ludwika Rydygiera w Bydgoszczy; study approval reference number KB 111/2014). Each patient will provide a written informed consent to participate in the study.

### Pharmacokinetics

Blood plasma concentrations of ticagrelor and AR-C124910XX will be evaluated using liquid chromatography mass spectrometry in samples obtained in eight predefined time points (Figure 2).

### Pharmacodynamics

Assessment of ticagrelor’s antiplatelet effects will be performed using up to four different methods (Figure 3). A platelet vasodilator-stimulated phosphoprotein (VASP) assay will be applied to all study participants at all predefined time points (Figure 2). Multiple electrode aggregometry (MEA) will be used at all predefined time points for all study participants with the exception of those treated with glycoprotein IIb/IIIa (GP IIb/IIIa) receptor inhibitors. VerifyNow and light transmission aggregometry (LTA) will be applied for at least 30% of all enrolled study participants at all predefined time points. Measurements with VerifyNow and LTA will not be performed in patients treated with GP IIb/IIIa receptor inhibitors. Details regarding methods to be used for the assessment of platelet reactivity were previously described [11-14].

**Figure 3 Fig3:**
[figure not shown]
Pharmacodynamic assessment schedule for IMPRESSION study. Legend: GP IIb/IIIa: glycoprotein IIb/IIIa; LTA: light transmission aggregometry; MEA: multiple electrode aggregometry.

### Treatment protocol and concomitant medications

During their participation in the study, all patients will be treated according to the current ESC guidelines. Administration of GP IIb/IIIa receptor inhibitors will be restricted to bailout situations. Interventional cardiologists will be encouraged to use manual thrombectomy in case of visible thrombus. The choice of the access of the coronary invasive procedure (radial or femoral) and the type of implanted stent (drug-eluting stent [DES] or bare metal stent [BMS]) will be at the discretion of the operator, although high rates of radial access and DES implantation are expected to occur. From the loading dose of ticagrelor until completion of the study, all patients will receive maintenance doses of ticagrelor (90 mg) twice daily. In addition, standard therapy will include aspirin (75 to 100 mg daily), beta blockers, statins, and angiotensin-converting enzyme inhibitors or angiotensin II receptor blockers, if not contraindicated.

### Study endpoints

The primary endpoint of this trial is the area under the plasma concentration-time curve (AUC_(0–12)_) for ticagrelor for the first 12 hours after the loading dose of ticagrelor. Secondary endpoints include AUC_(0–12)_ for AR-C124910XX, maximum concentration (Cmax) of ticagrelor and AR-C124910XX, time to Cmax for ticagrelor and AR-C124910XX, platelet reactivity index (PRI) assessed by VASP assay, area under the aggregation curve assessed by MEA, P2Y12 reaction units (PRU) assessed by VerifyNow, and ADP-induced platelet aggregation assessed by LTA.

### Safety

The following safety endpoints will be recorded: definite stent thrombosis according to the Academic Research Consortium criteria, major and minor, recurrent myocardial infarction according to the Third Universal Definition of Myocardial Infarction, all-cause death, stroke, and transient ischemic attack (TIA) according to definitions used in the PLATO trial, minor and major bleedings according to the BARC, PLATO, and TIMI criteria, dyspnea adverse events according to criteria used in the PLATO trial, bradyarrhythmic events according to criteria used in the PLATO trial.

### Statistics

Since there is no reference study examining the PK of ticagrelor in patients presenting with STEMI or NSTEMI, we decided to perform an internal pilot study of approximately 30 patients (15 patients for each arm) to estimate the final sample size. The means and standard deviations of AUC_(0–12)_ for ticagrelor in the first 33 patients assessed for patients who received morphine and for patients who received the placebo were 6,917 ± 4,920 and 10,379 ± 5,996 ng · h/ml, respectively. Based on these results and assuming a two-sided alpha value of 0.05, we calculated, using the *t*-test for independent variables, that enrollment of 68 patients would provide an 80% power to demonstrate a significant difference in AUC_(0–12)_ for ticagrelor between patients who received morphine prior to a loading dose of ticagrelor and those who received the placebo prior to the ticagrelor loading dose.

Continuous variables will be compared between both study arms by the Student’s *t*-test or the Mann–Whitney *U* test, depending on the presence or absence of the normal distribution (as assessed by the Kolmogorov-Smirnov test). Proportions will be compared by the Fisher exact test or chi-square test when appropriate. Pharmacokinetic calculations will be performed using a dedicated software.

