## Trial status

The first patient was enrolled in August 2014. Initially the IMPRESSION study was planned to include STEMI patients only. However, on 9 September 2014, after the approval of the Local Ethics Committee, the trial population was expanded to include subjects with NSTEMI as well. By 8 January 2015, 33% of planned patients were successfully included in the study. The baseline characteristics of the enrolled patients are presented in Table 2.

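### Sizing the trial at 68 from the arm difference in its first 33 patients, with an unadjusted final test, leaves the 5% error rate unsecured if enrolment ends below a pre-fixed 100; the 80% power is unsupported in any case

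*Protocol article*

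**What the plan says.** All three steps are in the Statistics section of the protocol article.

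- **Purpose of the pilot:** "we decided to perform an internal pilot study of approximately 30 patients (15 patients for each arm) to estimate the final sample size".
- **What was looked at:** AUC(0–12) of ticagrelor, which is the primary endpoint, "for ticagrelor in the first 33 patients assessed". The values for morphine and placebo "were 6,917 ± 4,920 and 10,379 ± 5,996 ng · h/ml, respectively".
- **How N was set:** "Based on these results and assuming a two-sided alpha value of 0.05, we calculated" that "enrollment of 68 patients would provide an 80% power to demonstrate a significant difference". No target difference is given from any other source.

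The same section says that continuous variables will be compared by Student's t-test or the Mann–Whitney test. It describes no allowance for the look.

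Two other places give a different size. The Abstract gives 100 as an upper limit. The Trial status section says "By 8 January 2015, 33% of planned patients were successfully included in the study"; with 33 patients in its baseline table, that is 33/100, whereas 33/68 would be 49%.

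**The concern.** An internal pilot that re-estimates only a nuisance SD hardly disturbs the error rate. One that re-estimates the effect does. A large early difference leads to a small trial, and the same early patients then carry a large share of the final test statistic. A small early difference leads to a larger trial in which they are diluted. Chance early differences in either direction are therefore kept at high weight when they are large, and the ordinary critical value does not account for this.

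The observed difference is also a fragile planning value. It comes from about 16 patients per arm, and nothing in the document says that it is the difference worth detecting. The sole primary test and the only stated justification of the sample size both rest on it.

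**Working it through.** **Inputs.** From the Statistics section: means 6,917 and 10,379, SDs 4,920 and 5,996, two-sided alpha 0.05, 80% power, N = 68, pilot of 33. From Study design and population: "Eligible patients will be randomly assigned in a 1:1 ratio to one of two study arms". From the Abstract: ceiling of 100. The pilot arm sizes are not given; I assume 16 morphine and 17 placebo.

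**1. The plan's own figure.** Difference = 10,379 − 6,917 = 3,462. Pooled SD = √[(4,920² + 5,996²)/2] = 5,484. Standardised difference d = 3,462/5,484 = 0.631.

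- Normal approximation: n per arm = 2(1.960 + 0.842)²/0.631² = 39.4, so 40 per arm and 80 in total.
- Noncentral t: 40 per arm gives 79.6% and 41 per arm gives 80.6%, so 82 in total.
- At 34 per arm: noncentrality 0.631 × √(34/2) = 2.60, critical value 1.997 on 66 df, power **72.7%**.

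So 68 is not reproduced. A one-sided test needs 64. The morphine SD alone gives 66, the placebo SD alone 98 and the mean of the SDs 82. A normal approximation on a simple log scale gives 68. None of these choices is documented.

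**2. How firm the pilot difference is.** With the 16/17 split the pooled SD is 5,502 and SE = 5,502 × √(1/16 + 1/17) = 1,916. Then t = 3,462/1,916 = 1.81 on 31 df and p = 0.08. The 95% CI is 3,462 ± 2.040 × 1,916, or −446 to 7,370. Splits from 15/18 to 18/15 keep p between 0.078 and 0.083.

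Power at 68 if the true difference is a fraction of the pilot difference:

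| True difference | d | Power at 68 | N for 80% |
|---|---|---|---|
| 100% | 0.631 | 73% | 82 |
| 75% | 0.473 | 49% | 144 |
| 50% | 0.316 | 25% | 318 |

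**3. Type I error.** The document gives no re-sizing rule, so one must be assumed. I simulated 1,000,000 trials under no effect with normal data and a pilot of 17 per arm. N was set for 80% power on the observed difference and SD, with a ceiling of 100, and all patients entered an unadjusted t-test.

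| Floor for N | Two-sided type I error |
|---|---|
| 38 (assumed) | 6.6% |
| 50 (assumed) | 6.2% |
| 68 (the document's figure) | 5.6% |
| N fixed at 100 | 5.0% |

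Repeat runs with other seeds differ by about 0.1 point. In the same setting, an inverse-normal combination of the two stages gives 5.0%, and re-estimating the SD alone against a pre-fixed difference gives 5.3%.

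**4. The pilot actually seen.** Converting t = 1.81 to a normal score gives z₁ = 1.75. If the remaining patients show no effect on average, the chance of a significant result is P(|√w·z₁ + √(1−w)·Z₂| > 1.96), where w is the pilot's share of N.

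- N = 68: w = 33/68, chance 15.0%.
- N = 100: w = 0.33, chance 12.2%.

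The gap is what is gained by choosing the smaller trial after a promising look.

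**The case against.** The strongest reply is that the document does not say that enrolment stops at 68. It says what 68 would provide, while the Abstract and Trial status still work from 100. If 100 was fixed beforehand and is kept, the look changed nothing and the ordinary test is valid. This stands, and it makes the error-rate point conditional. A reader might infer that the 5% level has already been lost; the documents do not support that. They do leave 68 and 100 unreconciled and call the pilot the means of estimating the final size, so the question is open.

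The size also needs restraint. Of the floors tried, only 68 is a number in the document, so 5.5–5.6% is the figure tied to the text and about 6.5% rests on floors that I supplied. The simulated rule does not reproduce 68 from the pilot data either, so it illustrates the mechanism and is not the sponsor's procedure.

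Retention of the 33 is nowhere stated outright. It follows from the word internal and from their being counted among the planned patients.

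A reader might also infer that treating staff were unblinded. The text shows only that results were computed by named arm and used for sizing; it does not say who saw them.

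Finally, any trial loses power if the effect is smaller than assumed, and the authors explain that they had no reference study. That is fair for the 49% and 25% figures. It does not answer the 72.7%, which uses their own effect. Nor does an unseen analysis plan answer the point, because the derivation of N is stated in this document.

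**Conclusion.** The point holds in a conditional form and should be fixed.

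- **Error rate:** N = 68 was derived from the observed arm difference, and the stated test takes no account of it. If the trial ends at a size chosen from that look, two-sided type I error is about 5.5–5.6% with N between 68 and 100, and about 6.5% with lower floors. This assumes normal data, retention of the 33 and an assumed re-sizing rule. With N fixed at 100 before the look and kept, it is 5.0%.
- **Power:** the 80% claim is unsupported without any such condition. The stated means and SDs give 72.7% at 68 and require 82 patients for 80%. The planning difference is not distinguishable from zero at the 5% level (p about 0.08, 95% CI about −446 to 7,370 with a 16/17 split).

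The excess error is modest. It matters because it falls on the only primary test and because the final N is unresolved.

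**What to change.** 1. **State one final N, and when the figure of 100 was set.** Reconcile the Abstract, Statistics and Trial status sections.
2. **If 100 predates the look,** choose one of two routes. Either keep N = 100 with the ordinary test, or stop earlier and test the primary endpoint with an inverse-normal combination, Z = √0.33·Z₁ + √0.67·Z₂. Z₁ comes from the first 33 patients and Z₂ from the later ones, against ±1.96. The stage p-values may come from the t-test or the Mann–Whitney test.
3. **If 100 does not predate the look,** use the combination test with weights fixed and documented now, before any second-stage results are seen by arm. Because the first stage is already known, the weights should not be tuned to it; equal weights are a neutral choice and held 5.0% in the simulation.
4. **Restate the power** at 68 as about 73% at the pilot difference, and show the 49% and 25% figures beside it.
5. **Disclose** in the trial report that arm means were seen at 33 patients and used for sizing.

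The cost is a short change of wording and one extra line of analysis. If the pilot difference is true, conditional power at 68 with the 0.33/0.67 weights falls by about 4 points, from about 80% to 76% with z₁ = 1.75, or from 81% to 77% if t is used as z₁. At 100 nothing is lost, but 32 more patients are needed than at 68.

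### The sample size does not follow from its own inputs: 68 patients give about 73% power, not 80%, and 80% needs about 82

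*Protocol article*

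**What the plan says.** The Statistics section of the protocol article explains that an internal pilot of about 30 patients was run to fix the final sample size, because no reference study was available. It reports ticagrelor AUC(0–12) "in the first 33 patients assessed". The means and SDs for the morphine and placebo arms "were 6,917 ± 4,920 and 10,379 ± 5,996 ng · h/ml, respectively".

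From these results, "assuming a two-sided alpha value of 0.05" and "using the *t*-test for independent variables", it concludes that "enrollment of 68 patients would provide an 80% power to demonstrate a significant difference". It mentions no dropout allowance, one-sided test, transformation or alternative SD.

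Allocation is fixed under Study design and population: "Eligible patients will be randomly assigned in a 1:1 ratio to one of two study arms". The Abstract gives a different number, a ceiling: "The study is planned to include up to 100 patients with myocardial infarction".

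**The concern.** Every input to the calculation is printed, so the result can be checked directly, and 68 looks too small for a standardised difference of about 0.63.

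This is the only power statement in the article, and it concerns the primary endpoint. The pilot was run to produce this number. If 68 is used as the recruitment target, the trial has less power against its own assumed effect than it claims. A non-significant primary result would then be weaker evidence against an interaction than the stated 80% suggests.

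**Working it through.** **Inputs** (Statistics section, except allocation, which is from Study design and population)

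- Morphine arm: mean 6,917, SD 4,920 ng·h/ml
- Placebo arm: mean 10,379, SD 5,996 ng·h/ml
- Two-sided alpha 0.05, target power 80%, independent-samples t-test
- 1:1 allocation, so 68 patients means 34 per arm

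**Effect size**

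- Difference: 10,379 − 6,917 = 3,462
- Common SD for equal arms: √[(4,920² + 5,996²)/2] = √30,079,208 = 5,484
- Standardised difference: d = 3,462/5,484 = 0.631

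**Attempt to reproduce 68**

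Normal approximation per arm:

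n = (1.96 + 0.8416)² × (4,920² + 5,996²)/3,462² = 7.849 × 60,158,416/11,985,444 = 39.4

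This rounds up to 40 per arm, 80 in total. The noncentral t gives 40.4 per arm, which rounds up to 41, or 82 in total. The figure of 68 is not reproduced.

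**Power at given sizes** (noncentral t, noncentrality d × √(n/2), 2n − 2 degrees of freedom)

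| Total | Per arm | Noncentrality | Power |
|---|---|---|---|
| 68 | 34 | 2.60 | 72.7% |
| 80 | 40 | 2.82 | 79.6% |
| 82 | 41 | 2.86 | 80.6% |
| 100 | 50 | 3.16 | 87.8% |

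At 68, the normal approximation gives 74.0% and the Welch version 72.7%. Welch also needs 82 for 80% power.

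**Other readings tried**

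| Reading | Total for 80% (t-test) | Power at 68 |
|---|---|---|
| Arithmetic mean of the two SDs (5,458) | 82 | 73.1% |
| SD pooled over pilot splits (morphine/placebo) from 12/21 to 20/13 | 86 down to 78 | 70.4% to 74.6% |
| Placebo SD in both arms | 98 | 65.0% |
| Morphine SD in both arms | 66 | 81.6% |
| One-sided 0.05, root-mean-square SD | 64 | 82.4% |

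The pilot split by arm is not reported, but across the splits tried it never brings power at 68 up to 80%. The one-sided reading contradicts the stated two-sided alpha. Reading 68 as per arm gives 95.5% power and a total of 136, above the ceiling of 100. A dropout allowance would push the total above 82, not below it.

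The closest two-sided match puts the smaller SD in both arms, which discards the reported placebo SD and still gives 66. An SD of about 5,020 in both arms would be needed for 80% power at 68, and no such value appears in the article.

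**The case against.** The strongest counter-argument concerns consequence, not arithmetic. The Abstract allows up to 100 patients. The Trial status section describes enrolment on 8 January 2015 as 33% of the planned number, and Table 2 shows 33 patients, which implies a plan of about 100. At 100, power on the article's own inputs is 87.8%, above the claimed 80%. This stands: the 27% miss rate applies only if the trial ends at 68. It does not settle the matter. The Abstract gives a ceiling rather than a commitment, the pilot was run to set the final size, and 68 is the only number tied to a power claim.

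A second point is that the inputs come from 33 patients, so the true power is uncertain by more than the gap between 73% and 80%. That is fair, and neither figure is a firm forecast. But the sentence says that 80% follows from these estimates, and it does not.

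A third possibility is analysis on the log scale. If AUC were log-normal with these means and SDs, the log-scale variances would be ln(1 + (4,920/6,917)²) = 0.409 and ln(1 + (5,996/10,379)²) = 0.288. The standardised difference would be about 0.79, and 68 patients would give about 89% power. That cannot justify the printed figure, because the article plans no log analysis and 89% is not 80% either.

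**Conclusion.** The stated figure is wrong. On the article's own inputs, 68 patients give 72.7% power and 80% needs 82 patients. The shortfall is 14 of 82, or 17%, and about 7 percentage points of power. If enrolment ends at 68, the type II error against the assumed effect is about 27% instead of 20%.

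This rests on equal arms, both reported SDs, a two-sided 5% t-test on untransformed AUC and no dropout, all as the Statistics and design sections have it. The conclusion survives a change between the exact t-test, Welch and the normal approximation, and any plausible pilot split. How much it matters in practice depends on whether 68 or about 100 is the recruitment target, and the article does not say.

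**What to change.** Correct the sentence in the Statistics section in one of two ways:

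1. Keep 68 and state that it gives about 73% power for the untransformed t-test.
2. State that 82 patients (41 per arm) give 80% power.

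In either case, print the SD and standardised difference used (5,484 and 0.631). Also state whether 68, 82 or 100 is the enrolment target, so that the Abstract, Statistics and Trial status sections agree. If the primary analysis is moved to another scale, recompute the size on that scale.

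The cost is small. The first option is a change of wording and a less favourable power figure. The second adds 14 patients to the stated number and stays inside the ceiling of 100.

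### The primary AUC(0–12) comparison is fixed as an unadjusted two-sample test although the trial pools STEMI and NSTEMI; a term for infarct type costs one degree of freedom and may gain precision

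*Protocol article*

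**What the plan says.** - **Endpoint** (Study endpoints): "The primary endpoint of this trial is the area under the plasma concentration-time curve" for ticagrelor over the 12 hours after the loading dose. This is a continuous variable.
- **Analysis** (Statistics): "Continuous variables will be compared between both study arms" by Student's t-test or the Mann–Whitney U test, chosen by a normality test. No covariate or stratum is named.
- **Sample size** (Statistics): the pilot means and SDs for morphine and placebo "were 6,917 ± 4,920 and 10,379 ± 5,996 ng · h/ml, respectively". "assuming a two-sided alpha value of 0.05" and using an independent-samples t-test, the article states that "enrollment of 68 patients would provide an 80% power". Both infarct types are pooled.
- **Population** (Trial status): "Initially the IMPRESSION study was planned to include STEMI patients only"; on 9 September 2014, about a month after the first enrolment, "the trial population was expanded to include subjects with NSTEMI as well". Table 2 shows 22 STEMI and 11 NSTEMI among the first 33.
- **Allocation** (Study design and population): "Eligible patients will be randomly assigned in a 1:1 ratio to one of two study arms". Nothing is said for or against stratification.
- **Enrolment ceiling** (Abstract): up to 100 patients.

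**The concern.** The widening of the population made infarct type an obvious baseline factor. Table 2 shows that the two groups are different kinds of patient: hypertension 31.8% in STEMI against 72.7% in NSTEMI, prior PCI 4.5% against 45.5%. If ticagrelor exposure also differs by infarct type, two things follow from an unadjusted comparison.

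- The between-type variation stays in the error term and costs power.
- If one arm happens to receive more NSTEMI patients, the observed arm difference moves accordingly and the planned test does not correct it.

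The point does not rest on the article's silence. The article names the tests for all continuous variables, and neither test can carry a covariate.

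**Working it through.** **Inputs.** From Statistics: means 6,917 (SD 4,920) and 10,379 (SD 5,996) ng·h/ml, two-sided alpha 0.05, 68 patients. From Table 2: NSTEMI share 11/33 = 1/3. From the Abstract: up to 100 patients.

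**Step 1. The plan's own figure.**
Difference = 10,379 − 6,917 = 3,462. Common SD = √[(4,920² + 5,996²)/2] = 5,484.
n per arm = 2 × (1.960 + 0.842)² × 5,484² / 3,462² = 39.4, so 40 per arm and 80 in total. The noncentral t gives 82.
The stated 68 is not reproduced. At 34 per arm the SE is 5,484 × √(2/34) = 1,330, the noncentrality is 3,462/1,330 = 2.603, and power is 72.7%. That shortfall is a separate matter; here 72.7% serves as the baseline.

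**Step 2. Power with infarct type in the model.** Let the types differ in mean AUC by k within-type SDs. This is an assumption, because the article gives no AUC by type. With one third NSTEMI:
R² = (2/9)k² / [1 + (2/9)k²], and SD(adj) = 5,484 × √(1 − R²).
Power is from the noncentral t with one degree of freedom fewer (65 at 68 patients, 97 at 100).

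| k | R² | SD(adj) | Power, 68 patients | Power, 100 patients |
|---|---|---|---|---|
| 0 | 0 | 5,484 | 72.7% | 87.8% |
| 0.2 | 0.009 | 5,460 | 73.1% | 88.1% |
| 0.5 | 0.053 | 5,338 | 75.0% | 89.4% |
| 0.8 | 0.125 | 5,132 | 78.2% | 91.6% |

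Unadjusted power is 72.7% at 68 patients and 87.8% at 100.

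**Step 3. Chance imbalance, if allocation was not stratified.** Each arm's NSTEMI count is taken as binomial with probability 1/3.

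| Arms differ in NSTEMI share by | 34 per arm | 50 per arm |
|---|---|---|
| at least 15 points | 15.6% of trials | 11.1% |
| at least 20 points | 9.4% | 4.3% |

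Fixing the total NSTEMI count at 22 to 24 of 68 instead (hypergeometric) gives 12–20% and 7–12%.

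At k = 0.5, a 15-point imbalance shifts the estimate by 0.15 × 0.5 × 5,338 = 400 ng·h/ml. That is 400/3,462 = 12% of the pilot difference, or 400/1,330 = 0.30 of a standard error.

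**Step 4. Validity.** Simulation with 34 per arm, 45 STEMI of 68, unstratified allocation and 10,000 trials per scenario:

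| Assumed type difference (ng·h/ml) | Type I error, unadjusted | Power, unadjusted | Power, adjusted |
|---|---|---|---|
| 0 | 5.1% | 72.4% | 71.6% |
| 2,000 | 4.9% | 72.5% | 73.3% |
| 4,000 | 5.0% | 73.6% | 78.0% |
| 6,000 | 5.0% | 73.0% | 84.6% |

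The 4,000 row is close to k = 0.8 and agrees with Step 2. In the zero row the adjusted model loses slightly under one point. The formula in Step 2 omits this small loss, which comes from imbalance in the covariate.

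**The case against.** The strongest reply is that nothing in the plan is invalid. Under randomization, chance imbalance is already part of the standard error; the simulated type I error stays at 4.9–5.1%. This stands. A reader might infer that the primary estimate is biased, and it is not.

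A reader might also infer that randomization was simple. The article says only 1:1, and a condensed article commonly leaves the method to the full protocol. If allocation was stratified by infarct type, the probabilities in Step 3 do not apply. The precision argument remains, because an unadjusted test would then ignore a stratification factor.

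Table 2 might be read as showing that the arms differ or that AUC depends on infarct type. It shows neither: it compares infarct types, not arms, and nothing in the article links hypertension or prior PCI to ticagrelor exposure.

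Nor does the expansion itself favour an arm. It came early and applied to both concurrently randomized arms.

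Finally, the gain may be close to nil, and it is smaller in points at 100 patients. The size of the trial is open: Trial status equates the patients so far with 33% of those planned, which with Table 2's 33 patients implies about 100. This too stands. It limits how much the point is worth, but does not remove the case for a change that costs so little.

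**Conclusion.** The point holds as one of efficiency. The article fixes an unadjusted comparison for its primary endpoint in a population that it has itself widened to two infarct types, and it leaves unused a factor known for every patient. Validity is not in question.

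The expected gain at 68 patients runs from nothing (or a loss of under one point) if the types have equal AUC, to about 2 points of power at 0.5 SD and 5 to 6 points at 0.8 SD. At 100 patients it is under 2 points at 0.5 SD. These figures assume the pilot means and SDs, one third NSTEMI, equal arms, and a type difference that the documents do not report. The gain is worth a little more because 68 patients give 72.7% power on the stated inputs, not 80%.

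**What to change.** Before unblinding, prespecify the primary analysis as a linear model of AUC(0–12) with terms for treatment arm and infarct type (STEMI/NSTEMI), reporting the adjusted arm difference with its confidence interval. Use the same model for the other continuous PK and PD endpoints. If a rank test is wanted, use one stratified by infarct type in place of the plain Mann–Whitney. State whether randomization was stratified by infarct type; if it was, the same model accounts for it.

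The cost is a change of wording and one degree of freedom. No new data are needed, because infarct type is established before randomization. The unadjusted test can be kept as a sensitivity analysis.
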